## Sample recruitment process

### Study setting

The study will be conducted at Mercatorum University, a private Italian online university. Due to the online nature of Mercatorum University, the psychological counseling interventions and the related research activities will be carried out online (in videoconference), in the context of the psychological counseling service of the university and using Google Meet links provided in the University Web Platform.

### Participants and sample size

Assuming a medium effect size (Cohen's *d* = 0.50), we estimated with the G^*^Power3 software (Faul et al., 2007) that we need a sample size of 128 participants (i.e., two groups of 64 students) to achieve a power of 0.80 (α = 0.05). Thus, a total of 130 students will be recruited from bachelor's courses at Universitas Mercatorum. Participants are eligible for inclusion according with the following criteria: (a) age > 18 years; (b) clinical levels of academic burnout scores [one standard deviation above the mean MBI-SS total score reported in the validation study by Portoghese et al. (2018)]; (c) attendance of 1^st^ or 2^nd^ year of bachelor course at Universitas Mercatorum; and (d) sufficient knowledge of the Italian language. Additional exclusion criteria aimed at selecting a sufficiently homogeneous group of participants are: (a) previous university degree; (b) other psychiatric diagnoses; (c) other ongoing psychological or psychiatric treatments. Finally, we also excluded (d) attendance of 3^rd^ year of bachelor course, to avoid participants drop-outs due to the course conclusion.

## Instruments

### Screening instruments

#### Maslach burnout inventory-student survey

The MBI-SS (Schaufeli et al., 1996; Italian adaptation: Portoghese et al., 2018) is a 15-item self-report questionnaire composed of three subscales: Exhaustion (EX; item example “*I feel used up at the end of a day at university*”), Cynicism (CY; item example “*I doubt the significance of my studies*”), and Professional Efficacy (PE; item example “*During class I feel confident that I am effective in getting things done*”). All the items are scored by using a 7-point Likert scale ranging from 0 (=“*never*”) to 6 (=“*always*”). We will use the Italian version of MBI-SS from the study of Portoghese et al. (2018), in which reliability coefficients for each of the subscale scores were 0.86 for EX, 0.82 for CY and 0.77 for PE. The MBI-SS will be used to select students with high levels of academic burnout.

#### Personal information and eligibility form

This form was developed to collect information about the demographic characteristics of the students participating in the study. The form contains a total of 10 questions regarding basic personal information (sex, age, previous experience of psychological counseling/psychotherapy, current, or previous psychological/psychiatric diagnoses), educational information (attended bachelor course, previous academic experience, previous academic degree, and parents' education), and economical status (current economic situation and economic situation in childhood).

### Primary outcomes measures

#### Maslach burnout inventory-student survey

The MBI-SS will be also used as primary outcome measure.

#### Psychological general wellbeing index–short version

The PGWB is a self-report measure of intra-personal affective or emotional states, which captures a subjective perception of wellbeing referring to the last 4 weeks (original version: Dupuy, 1984; Italian short-form version: Grossi et al., 2006). It is composed by items assessing Anxiety, Depressed Mood, Positive Wellbeing, Self-Control, General Health, and Vitality (item example “*How much energy, pep, or vitality did you have or feel during the past month?*”). All the items are scored by using a 6-point Likert scale ranging from 0 (for example “*Very full of energy–lots of pep*”) to 6 (for example “*No energy or pep at all–I feel drained, sapped*”).

#### Academic achievement

The academic achievements of the students participating to the study will be measured based on the self-reported number of passed exams and the average exam grades. Moreover, self-reported satisfaction in academic achievement will be also assessed with a 4-point Likert scale item ranging from 1 (=“*not satisfied*”) to 4 (=“*completely satisfied*”).

### Mediational measures

#### Basic psychological need satisfaction and frustration scale

The BPNSFS is a self-report general measure of the satisfaction and frustration of the psychological needs in one's life (Italian adaptation: Costa et al., 2018; Cardella et al., 2020). It is composed of the following subscales: Autonomy Satisfaction (item example “*I have a feeling of choice and freedom in what I do at work”*), Competence Satisfaction (item example “*I feel confident that I can do things well at work*”), Relatedness Satisfaction (item example “*I feel closely connected to other people who are important to me at work.”*), Autonomy Frustration (item example “*My daily activities at work feel like a continuous line of duties*”), Competence Frustration (item example “*I seriously doubt whether I can do things well at work ”*), and Relatedness Frustration (item example “*I feel that the relations I have at work are only superficial”*). All 24 items are scored on a 5-point Likert-scale ranging from 1 (=“*completely disagree*”) to 5 (=“*completely agree*”).

#### Effort-reward imbalance student questionnaire

The ERI-SQ is a self-report measure to identify effort-reward imbalance in university students (Wege et al., 2017; Italian adaptation: Portoghese et al., 2019). It is composed of the following subscales: Effort (item example “*I have constant time pressure due to a heavy study load”*), Reward (item example “*I receive the respect I deserve from my supervisors (teachers”*), and Over-Commitment (item example “*Student work rarely lets me go; it is still on my mind when I go to bed”*). All the items are scored by using a 4-point Likert scale ranging from 1 (=“*strongly disagree*”) to 4 (=“*strongly agree*”).

#### Cognitive emotion regulation questionnaire-short version

The CERQ-18 is a self-report measure of cognitive emotion regulation strategies individuals may use after experiencing negative life events (Garnefski and Kraaij, 2006; Italian adaptation: Cerolini et al., 2022). It evaluates the habitual use of Self-Blame (item example “*I feel that I am the one to blame for it”*), Other-Blame (item example “*I feel that others are to blame for it”*), Rumination (item example “*I often think about how I feel about what I have experienced”*), Catastrophizing (item example “*I often think that what I have experienced is much worse than what others have experienced”*), Putting Into Perspective (item example: “*think that other people go through much worse experiences”*), Positive Refocusing (item example “*I think of something nice instead of what has happened”*), Positive Reappraisal (item example “*I think I can learn something from the situation”*), Acceptance (item example “*I think that I have to accept that this has happened”*), and Refocus on Planning (item example “*I think about how I can best cope with the situation”*). All 18 items are scored on a 5-point Likert-scale ranging 1 (=“*almost never*”) to 5 (=“*almost always*”).

#### Difficulties in interpersonal emotion regulation

The DIRE is a self-report measure of maladaptive interpersonal emotion regulation strategies that may relate to psychopathology (Dixon-Gordon et al., 2018; Italian adaptation: Messina et al., 2022). It is composed of the following subscales: Venting (item example “*Raise your voice or criticize your friends to express how you feel”)*, Reassurance-Seeking [item example “*Keep contacting (texting, calling, etc.) friends and loved ones”*], Avoidance (item example “*Avoid feeling or showing your distress”*), and Acceptance (item example “*Simply notice your feelings”*). All 21 items are scored on a 5-point Likert-scale ranging from 1 (=“*very unlikely*”) to 5 (=“*very likely*”).

#### Coping orientation to problems experienced (Brief-Cope)

The Brief-Cope is a self-report measure of different coping reactions (Carver et al., 1989; Italian adaptation Bongelli et al., 2022). It includes the following subscales: Problem-Focused Coping (item example “*I've been trying to come up with a strategy about what to do”*), Emotion-Focused Coping (item example “*I've been getting emotional support from others”*), and Avoidant Coping (item example “*I've been using alcohol or other drugs to make myself feel better”*). All 28 items are scored on a 5-point Likert-scale ranging from 1 (=“*I haven't been doing this at all”*) to 4 (=“*I've been doing this a lot*”).

#### The multidimensional scale of perceived social support

The MSPSS is a self-report measure of perceived emotional support (Zimet et al., 1988; Italian Adaptation Cipolletta et al., 2022). Perceived social emotional support is evaluated over three dimensions: Family (item example “*My family really tries to help me”*), Friends (item example “*I can count on my friends when things go wrong”*), and Significant Others (item example “*I have a special person who is a real source of comfort to me”*), with each subscale containing four items. All the items are scored by using a 7-point Likert scale ranging from 1 (=“*strongly disagree*”) to 7 (=“*strongly agree*”).

### Other outcome variables

Together with self-rated improvements, additional indicators of outcome will be considered. First, acceptance rate will be calculated by taking the total number of participants who accepted, agreed, and consented to participate in this study and dividing it by the number of participants who were invited to participate. Second, adherence rate will be calculated as the total number of participants who completed the intervention according to the study protocol divided by the number of participants who started the intervention. Third, dropout rate will be calculated as number of participants who withdrew from or did not continue the intervention divided by the number of participants who consented to participate on the study.

## Procedures

The study will entail the following phases: (T0) Screening, Recruitment and Randomization; (T1) Baseline assessment (pre-intervention); (T2) Outcome Assessment (post-intervention); and (T3) Follow-up Assessment (3 months after the intervention). A summary of study design procedures is showed in Figure 1.

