## Abstract

Academic burnout is a condition characterized by exhaustion, cynicism, a distant attitude toward studying, and diminished self-efficacy in academic activities. Preliminary scientific findings indicate that interventions designed to alleviate work burnout also hold promise for mitigating academic burnout, however clear evidence based on randomized controlled trials is still missing. This research protocol describes a randomized controlled trial aimed at evaluating the efficacy of an online group psychological intervention to contrast academic burnout. Participants with high levels of burnout will be assigned to a psychological counseling group or a waiting list control group. The research comprises several phases: (T0) Screening, Recruitment, and Randomization; (T1) Baseline assessment (pre-intervention); (T2) Outcome Assessment (post-intervention); and (T3) Follow-up Assessment (3 months post-intervention). The primary outcomes include burnout symptoms, general wellbeing, and academic achievement. Additionally, secondary variables such as effort-reward imbalances, satisfaction/frustration of basic psychological needs, intrapersonal and interpersonal emotion regulation, coping strategies, and social support will be examined. The psychological intervention strategies will encompass psychoeducation, self-awareness enhancement, cognitive restructuring, and promotion of social support. This research protocol is an initial step toward evidence-based psychological interventions to treat academic burnout.

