### Screening and recruitment

Potential participants will be invited electronically via email to students' listservs, on a weekly basis until target enrolment will be reached. In this e-mail, potential participants will receive written information on the screening aims and those who provide written consent with screening participation will fill out the PIEF and the MBI-SS. Eligible participants identified in the screening phase will be contacted by a researcher and invited to a brief assessment interview to further evaluate their eligibility based on a psychologist's rating, to give oral and written information about the clinical trial and obtain informed consent to the clinical training. Then, participants will be randomized to PC or WL groups by a colleague not involved in the study, using a computerized randomization generator. The research team will be blind to the randomized allocation.

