### Outcomes data collection

Outcome variables will be assessed at T1, T2, and T3, using a Google Form. At each time, participants of the two groups will be required to fill in the eight self-report questionnaires described above (MBI-SS, PGWB-S, BPNSFS, ERI-SQ, CERQ-18, DIRE, Brief-Cope, and MSPSS). Baseline data (T1) will be collected after brief assessment interview (once informed written consent has been obtained by the participant). T2 data will be collected after the end of the last PC session. Finally, 3 months after the end of PC, participants will be contacted electronically via email and invited to fill in the Google Form to obtain T3 data.

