### Statistical analysis

Descriptive statistics will be reported for participant recruitment, acceptance, adherence, and dropout rates. Baseline characteristics for each group will be reported to ensure group matching on these variables. To verify the reliability of the eight questionnaires, we will compute test-retest correlations between T1 and T2, and between T1 and T3 (using Pearson's *r* coefficients).

To assess the effects of PC on the outcome variables (MBI-SS, PGWB-S, and academic achievement), mixed model regressions will be utilized, by considering Time (T1, T2, and T3) and Group (PC vs. WL) as fixed factors and subjects as the random factor. This technique will allow us to test the interaction between Time and Group. Our expectation is that PC and WL should differ at T2 and T3, but not at T1, indicating that the PC group should achieve higher scores than the WL group after, but not before, the psychological counseling intervention.

A series of path analyses will be conducted to determine whether the measures obtained from the BPNSFS, ERI-SQ, CERQ-18, DIRE, Brief-Cope, and MSPSS questionnaires mediate the differences in the outcome variables between T1 and T2, and T1 and T3. For each analysis, the exogenous variables will be the outcome measures at T1, the mediators will be the scores in the subscales of the BPNSFS, ERI-SQ, CERQ-18, DIRE, Brief-Cope, and MSPSS questionnaires, and the endogenous variables will be the outcome measures at T1. Since each questionnaire involves multiple subscales, two separate models will be computed for each mediator. For example, for the BPNSFS questionnaire, we will test whether the Autonomy Satisfaction, Competence Satisfaction, Relatedness Satisfaction, Autonomy Frustration, Competence Frustration, and Relatedness Frustration subscales will mediate the associations between the T1 and T2 (or T1 and T3) outcome measures.

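### Randomization is listed before the self-reported baseline (T1), nothing places T1 before students learn their arm, and the model leaves the arms free to differ at T1

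*Protocol article*

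**What the plan says.** The order of steps is given twice in the same way. The Abstract has "T0) Screening, Recruitment, and Randomization; (T1) Baseline assessment (pre-intervention" and Procedures has "T0) Screening, Recruitment and Randomization; (T1) Baseline assessment (pre-intervention". Both put randomization in the phase before baseline.

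Screening and recruitment describes the interview and consent and continues: "Then, participants will be randomized to PC or WL groups by a colleague not involved in the study". On blinding it says only this: "The research team will be blind to the randomized allocation". It says nothing about when students are told their arm.

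Outcomes data collection gives the timing of T1 as follows: "Baseline data (T1) will be collected after brief assessment interview (once informed written consent has been obtained by the participant". That sets the earliest point for T1 but does not place it before or after randomization. The same section gives the mode: "Outcome variables will be assessed at T1, T2, and T3, using a Google Form".

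Statistical analysis specifies mixed models "by considering Time (T1, T2, and T3) and Group (PC vs. WL) as fixed factors and subjects as the random factor", and adds: "This technique will allow us to test the interaction between Time and Group". T1 is therefore one level of the response, with its own group difference. The text expects that difference to be absent but does not impose this in the model.

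**The concern.** A baseline is protected by randomization only if it is measured before allocation can influence it. The T1 measures are self-reports. A student who knows that counseling is about to start, or that the wait is several months, may answer burnout and wellbeing items differently, and a wait-listed student may not return the form. The interaction contrasts subtract T1, so a shift of that kind becomes part of the estimated effect.

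The MBI-SS taken at screening does not settle this. Students are selected on that score, and the planned model starts at T1. No pre-randomization measure of wellbeing is described.

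The second issue is precision and stands apart from the first. If T1 is a true baseline, the arms share one T1 mean by design. Spending a parameter on a T1 group difference then discards information, in a trial that recruits 130 against a calculated 128.

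**Working it through.** **Order of steps.** Abstract and Procedures: randomization in T0, then T1. Screening and recruitment: interview, consent, then randomization. Outcomes data collection: interview, consent, then T1. The first pair puts T1 after randomization. The last two are compatible with T1 on either side of it. None gives the time of disclosure.

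**Inputs.** From Participants and sample size: d = 0.50, alpha = 0.05, power 0.80, 64 per arm (65 per arm planned). Not in the document and therefore assumed: the correlation rho between repeated measures (ranged), equal variances over time, complete data, and a two-sided test.

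**The plan's own figure.** A two-sided two-sample t-test with d = 0.50 and power 0.80 needs 63.77, so 64 per arm and 128 in total. Power is 0.801 at 64 and 0.808 at 65 per arm. The stated 128 is reproduced.

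**Effect of a T1 shift.** Let knowledge of allocation move the arm difference at T1 by b SD.
- T2-T1 contrast: biased by the full b. An illustrative b = 0.1 is 0.1/0.50 = 20% of the assumed effect.
- T1 as covariate, or a common T1 mean: biased by rho × b, which is 0.05 SD for b = 0.1 and rho = 0.5.
- Plain T2 difference with complete data: not affected.

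**Precision.** Variance of the T2 group contrast, in units of 2·SD²/n:
- T1 free, T2-T1 contrast: 2(1-rho)
- plain T2 difference: 1
- T1 as covariate or common T1 mean: 1-rho²

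The ratio of adjusted to free is (1-rho²)/[2(1-rho)] = (1+rho)/2. A generalized least squares calculation with three time points and compound symmetry gave the same variances at rho 0.3, 0.5 and 0.7.

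Dividing d by the square root of each variance gives the effective effect size, and the t-test then gives power at 64 per arm:

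| rho | (1+rho)/2 | effective d, free | effective d, adjusted | power, free | power, adjusted |
|---|---|---|---|---|---|
| 0.4 | 0.70 | 0.456 | 0.546 | 0.73 | 0.87 |
| 0.5 | 0.75 | 0.500 | 0.577 | 0.80 | 0.90 |
| 0.6 | 0.80 | 0.559 | 0.625 | 0.88 | 0.94 |
| 0.7 | 0.85 | 0.645 | 0.700 | 0.95 | 0.98 |

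The plain T2 difference has power 0.80 whatever rho is, so it too is less precise than the adjusted contrast.

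**The interaction as planned.** Time has three levels, so the overall interaction test has 2 degrees of freedom. If d = 0.50 at both T2 and T3 under compound symmetry, the noncentrality is n·d²/[3(1-rho)]. With n = 64 this is 16/[3(1-rho)]: 8.89, 10.67 and 13.33 at rho 0.4, 0.5 and 0.6. Power is about 0.76, 0.84 and 0.91, which is above the single free contrast and below the adjusted one.

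**The case against.** The strongest reply is that the bias needs students to know their arm when they answer T1, and the document does not say that they do. T1 taken straight after consent fits the recruitment and data collection sections. A colleague outside the study generates the allocation, so generation and disclosure may be separate events. This stands: what the text shows is an order stated the wrong way round and a disclosure time left open. A reader might infer that unblinded students demonstrably distorted the baseline, but the document does not support that.

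A reader might also infer that every primary and mediation analysis is affected. The path analyses as described have no Group term, so this mechanism does not reach them. The argument is made for burnout and wellbeing items. It gives no reason why being wait-listed would change the number of exams passed or the average grade.

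Nor does a T1 shift enter every contrast. The stated expectation is that the arms differ at T2 and T3, and with complete data a plain difference at those times does not subtract T1. The interaction that the plan names as its test does.

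On the model, a Time by Group mixed model is valid and in common use, and the more efficient form is a choice rather than the correction of an error. That is fair. It is still worth making, because the gain holds against both the interaction contrast and the plain T2 difference. A reader might take the power figures to mean that 128 is too few. They do not show this: rho is unknown, and from 0.5 upward even the free contrast reaches 0.80. Finally, the plan does not explicitly specify a test for a T1 difference, so there is no such test to remove.

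**Conclusion.** The point holds in limited form. The protocol places randomization before a self-reported baseline in two sections, and no section places T1 before students learn their arm. If T1 follows disclosure, the T2-T1 and T3-T1 contrasts for burnout and wellbeing could be biased by the full T1 shift, and T1 could be lost selectively in the wait-list arm. The size cannot be estimated from the document, and the 0.1 SD shift above is only illustrative.

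The loss of precision follows from the model as written if T1 is a true baseline. The adjusted variance is 70% to 85% of the free contrast's for rho from 0.4 to 0.7. The gain in power is about 14 percentage points at rho 0.4 (0.865 against 0.727) and 10 at rho 0.5, but only 2 to 3 at 0.7. These figures assume complete data, equal variances and a single post-baseline contrast.

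The two parts are linked. A common T1 mean is fully justified only once T1 precedes disclosure. If it does not, adjusting for T1 would carry rho × b of any shift into the estimate.

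**What to change.** 1. Require the T1 form to be submitted before the allocation is generated and disclosed, and say so under Outcomes data collection. Move randomization after T1 in the Abstract and Procedures, and in Figure 1 if it shows the same order. If T1 is already taken first in practice, one clarifying sentence together with the corrected order is enough.
2. Given step 1, fit the mixed model with a common T1 mean for the two arms, or with T1 as covariate and T2 and T3 as responses. Report the difference between counseling and waiting list at T2 and at T3 as the treatment effect.

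The cost is the order of two online steps and one line of the model. The downside is that the T1 form has to be chased before a student can be allocated.
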